### Process Evaluation

To gain an insight into the process-related factors that may have influenced the effectiveness of the 3-week analogy learning walking intervention, a process evaluation will take place along the study [55]. Data will be collected to (1) asses to what extent the therapists delivered the interventions as intended (fidelity), (2) explore the therapists’ opinions and experiences about the interventions with regard to the feasibility and possible effects, and (3) explore the patients’ opinions and experiences about the interventions with regard to the feasibility. Table 2 represents the data collection methods used to assess the different aspects of the process evaluation. For both groups, the provided instructions will be documented and evaluated in the therapists’ logs. In addition, short questionnaires will be used to administer the therapists’ and participants’ opinions about the gait training after the completion of the 3-week intervention. To explore the extent to which the interventions were implicit or explicit in nature, the verbal protocol will be assessed. Evidence indicates that implicit learning is typically characterized by the less accumulation of explicit rules compared with explicit learning [24,56].

To monitor the integrity of the intervention, self-reported (subjective) and audio-recorded (objective) data will be evaluated. First, all therapists are required to self-report any deviations from the treatment protocol or other incidents during the session in a log after every session. All instructions used during therapy sessions will be recorded in the therapists’ and patients’ logs. Furthermore, patients can use the log to write down any possible events that might have occurred during unguided therapy. The patient log is, therefore, only used as a reminder for unguided therapy and as a communication tool between therapists and participants. Second, 10 gait trainings will be randomly selected (5 implicit and 5 explicit interventions) and audio recorded. Both self-reported and audio-recorded data will be screened to evaluate whether the intervention was delivered according to the protocol.

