### Sample Size

The sample size calculation is based on a randomized controlled trial with equal group sizes and “walking speed” (10-meter walking test, 10MWT) as a primary outcome measure [30]. The power is set at beta=.80, the significance level at alpha=.05, and a standard deviation of 0.23 m/s [31]. To demonstrate a significant change in walking speed, the minimal clinically important difference (MCID) is used and set at a minimum change of 0.16 m/s [32,33]. The calculations resulted in a minimum group size of 33 participants per group. Taking into account that 20% (7/33) of participants may be lost during (dropout) and after the intervention (loss to follow-up), this study aims to recruit 40 participants per group.

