### Data Analyses

Baseline scores of demographic and prognostic data and primary and secondary outcome measures will be used to compare the 2 groups. Only data of the participants who attended minimum of 7 or more of the therapy sessions will be considered as adherent and processed in the statistical analysis. Statistical analysis will be conducted to determine significant differences between groups and over time (baseline and postintervention performance). A repeated measure analyses will be used to compare the 2 groups (implicit and explicit) at 3 different time points (before, after, and after 1-month follow-up). Post hoc tests with correction for multiple testing will be used to explore effects over time and between groups. Subgroup analysis will be performed on cognition (MoCA score <21) [35]. An alpha level of .05 will be set for all tests. The primary outcome measure, walking speed, will also be described with reference to clinically relevant differences between groups (MCID: 0.16 m/s) [33]. All datasets used or analyzed during this study are available from the corresponding author on a reasonable request.

Data will be analyzed according to an intention-to-treat and per-protocol principle. In the intention-to-treat, data of the participants are analyzed according to their original treatment allocation. If self-reported (subjective) and audio-recorded (objective) data reveal that cases are not delivered as intended, then the analyses will be performed using the per-protocol principle. Within this study, protocol deviations are defined as “deviations from the protocol that occur in two or more sessions.” If protocol deviations were observed, then data from this person were not included in the per-protocol analysis. Data in the process evaluation related to the therapists’ and patients’ opinions and experiences toward the feasibility of the intervention and perceived benefits will be analyzed by means of descriptive statistics. Free comments and clarifying examples may be quoted and used to describe personal experiences of the therapists or participants.

**Table 2 table2:** Measures for the process evaluation. A checkmark indicates with which measure the question is examined.

Questions	Measures			
	Therapist Log	Audio recordings	Therapist questionnaire	Patient questionnaire
To what extent did the therapists deliver the interventions as intended (fidelity)?	✓	✓	✓	

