How did the therapist’s experience delivering the interventions with regard to the feasibility and possible effects?			✓	
How did the patients’ experience the intervention with regard to the feasibility?				✓

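### Patient-rated feasibility rests on one questionnaire timed after the 3-week training, with no stated route to the views of participants who stop earlier

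*Protocol article*

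**What the plan says.** The Process Evaluation section sets three aims, one of which is to explore patients' views on feasibility. On timing, it has short questionnaires record the therapists' and "participants’ opinions about the gait training after the completion of the 3-week intervention".

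Table 2, under Data Analyses, assigns measures to questions. For the question "How did the patients’ experience the intervention with regard to the feasibility" the only tick is the patient questionnaire. The therapist log and the audio recordings are ticked for fidelity only.

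Two logs run during training. For the therapist log, "all therapists are required to self-report any deviations from the treatment protocol or other incidents during the session in a log after every session". The other belongs to the participant, and its role is limited: "The patient log is, therefore, only used as a reminder for unguided therapy and as a communication tool between therapists and participants".

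The Sample Size section allows that "20% (7/33) of participants may be lost during (dropout) and after the intervention (loss to follow-up"), and recruits 40 per group. The loss is not split into a part during training and a part afterwards.

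Data Analyses says that opinions on "feasibility of the intervention and perceived benefits will be analyzed by means of descriptive statistics". It names no population or denominator for these data.

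**The concern.** A feasibility questionnaire is most informative about the people for whom the training was least workable. If it is given only when the three weeks are over, a participant who stops after two sessions may not be there to fill it in. The answers would then come mainly from people who found the training manageable enough to finish, so the result would depend partly on the thing being measured.

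The process evaluation is meant to help explain what influenced effectiveness. Stopping because the training did not suit is one such influence. If the numbers stopping turned out to differ between arms, the plan as described would hold no participant account of why.

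**Working it through.** **Step 1: can stoppers' views arrive by another route?**

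| Source | When | What it captures | Participant's view of feasibility? |
|---|---|---|---|
| Patient questionnaire | After the 3 weeks | Opinions on the training | Yes, the only tick in Table 2 |
| Therapist log | After every session | Deviations and incidents | No, assigned to fidelity |
| Audio recordings | 10 selected sessions | Delivery of the intervention | No, assigned to fidelity |
| Patient log | During training | Reminder and communication aid | No, by its stated role |
| Global Perceived Effect scale | T2 in Table 1 | Change in walking ability | No, and later still |

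No listed source is assigned to a participant's reason for stopping.

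**Step 2: the plan's own loss figure.** 33 × 1.20 = 39.6, which rounds up to the planned 40 per group. A 20% loss from 40 is 8 participants, leaving 32. These 8 include people lost after training, so 8 per arm is an upper value for those who stop during training under the plan's assumption.

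**Step 3: size of the possible bias.** Let d be the share of an arm not asked, p the favourable share among those asked, and q the favourable share among those not asked.

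- Share reported: p
- Share in the whole arm: (1 − d)p + dq
- Overstatement: p − [(1 − d)p + dq] = d(p − q)

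The documents give neither p nor q, nor the during-training part of the loss. All three are assumed here, with q no larger than p.

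| d | p | q | Whole-arm share | Overstatement (points) |
|---|---|---|---|---|
| 5% | 80% | 0% | 76% | 4 |
| 5% | 80% | 50% | 78.5% | 1.5 |
| 10% | 80% | 0% | 72% | 8 |
| 20% | 80% | 0% | 64% | 16 |
| 20% | 80% | 50% | 74% | 6 |
| 20% | 90% | 0% | 72% | 18 |
| any | any | equal to p | p | 0 |

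Over d from 5% to 20%, p from 70% to 90% and q from 0 to p, the range is 0 to 18 points. The top of the range needs all the planned loss to fall during training and every stopper to be negative. If stoppers were more favourable than completers (q above p), the sign would reverse.

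**The case against.** The strongest reply is that the sentence fixes a time and not a population. The three weeks can be read as a calendar period, at the end of which everyone, including those who stopped, could receive the form. Nothing in the article excludes stoppers. How withdrawn participants are approached is also a detail that an article often leaves to the full protocol. This stands against one tempting reading, that stoppers are never asked and that feasibility is therefore overstated. The documents support only that they may not be asked and that the result may be too favourable. It does not dispose of the point, because the timing is a choice the article states, and it is the timing that creates the risk.

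Other inferences a reader might draw also fail:

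- **That therapists' views are affected in the same way.** A therapist can still report on someone who stopped, logs every session, and attends three evaluation sessions during the trial where difficulties are discussed.
- **That the 7-session adherence rule removes stoppers from the questionnaire.** That rule is stated for the statistical analysis and is not extended to the opinion data.
- **That stopping will differ by arm.** The explicit arm aims for many verbal instructions, but the article also says that both conditions are adapted to what the participant can manage. It gives no reasons for stopping and no rates by arm.
- **That a planned percentage will be wrong by a known amount.** No feasibility percentage or threshold is planned. Opinions are summarised descriptively, with free comments.

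**Conclusion.** The point holds as a minor one. The only measure of patient-rated feasibility is timed after the training, the article describes no other route to the views or reasons of participants who stop, and it foresees some dropout during training. The descriptive results may therefore reflect mainly completers.

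The direction is plausible but not certain, and the size cannot be determined from the documents. The 0 to 18 point range rests on assumed values for the share not asked and for the favourable shares among those asked and not asked. The primary walking-speed comparison and its sample size are not affected.

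**What to change.** Amend the timing sentence in Process Evaluation so that the participant questionnaire is given at the end of training or when a participant stops, whichever comes first, and add one item on the main reason for stopping.

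Add to Data Analyses that the following are reported for each arm: numbers randomised, stopped (with reasons), asked and answering. Show feasibility among respondents. Do not use all randomised participants as the denominator, because that counts every non-responder as finding the training not feasible. For example, if 29 of 32 respondents were favourable and 8 did not reply, 29/32 = 91% would become 29/40 = 73% whatever those 8 thought.

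The cost is one sentence, one questionnaire item, and a call or posted form for at most about 8 participants per arm under the planned loss. Some will not reply, so the change reduces the selection without removing it. The response counts let a reader judge what remains.

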### Data Analyses

Baseline scores of demographic and prognostic data and primary and secondary outcome measures will be used to compare the 2 groups. Only data of the participants who attended minimum of 7 or more of the therapy sessions will be considered as adherent and processed in the statistical analysis. Statistical analysis will be conducted to determine significant differences between groups and over time (baseline and postintervention performance). A repeated measure analyses will be used to compare the 2 groups (implicit and explicit) at 3 different time points (before, after, and after 1-month follow-up). Post hoc tests with correction for multiple testing will be used to explore effects over time and between groups. Subgroup analysis will be performed on cognition (MoCA score <21) [35]. An alpha level of .05 will be set for all tests. The primary outcome measure, walking speed, will also be described with reference to clinically relevant differences between groups (MCID: 0.16 m/s) [33]. All datasets used or analyzed during this study are available from the corresponding author on a reasonable request.

Data will be analyzed according to an intention-to-treat and per-protocol principle. In the intention-to-treat, data of the participants are analyzed according to their original treatment allocation. If self-reported (subjective) and audio-recorded (objective) data reveal that cases are not delivered as intended, then the analyses will be performed using the per-protocol principle. Within this study, protocol deviations are defined as “deviations from the protocol that occur in two or more sessions.” If protocol deviations were observed, then data from this person were not included in the per-protocol analysis. Data in the process evaluation related to the therapists’ and patients’ opinions and experiences toward the feasibility of the intervention and perceived benefits will be analyzed by means of descriptive statistics. Free comments and clarifying examples may be quoted and used to describe personal experiences of the therapists or participants.

**Table 2 table2:** Measures for the process evaluation. A checkmark indicates with which measure the question is examined.

Questions	Measures			
	Therapist Log	Audio recordings	Therapist questionnaire	Patient questionnaire
To what extent did the therapists deliver the interventions as intended (fidelity)?	✓	✓	✓	
How did the therapist’s experience delivering the interventions with regard to the feasibility and possible effects?			✓	
How did the patients’ experience the intervention with regard to the feasibility?				✓

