#### Training of Therapists and Treatment of Participants

An intervention guideline is developed that outlines how the treatments (implicit and explicit conditions) should be delivered. The main aim of the intervention is to improve the quality of walking performance in people after stroke. The basic principle of the intervention guideline is based on the definitions of implicit and explicit motor learning by Kleynen et al [11]. For the purpose of this study, we strive to create the largest contrast between the conditions as possible. The main characteristics and differences in instructions, and feedback of the practice between interventions are described in Figure 1. Both conditions will always be applied to an extent that is feasible for the participant, and training will therefore always be tailored to the participant’s abilities within the given boundaries of the condition. Similar situations will be adopted in both conditions with regard to the “organization” of the training, for example, use variation in the (analogy) instructions and practice of the motor skill.

The chosen intervention period was based on a preliminary study of Kleynen et al [28] that demonstrated that 3 weeks was a feasible period to develop and practice analogies with people after stroke. All participants will receive 9 training sessions in a 3-week intervention period, that is, 3 training sessions per week (Figure 2). Each training session takes place at the home of the participants and lasts for 30 min. Participants were asked to use the instructions in daily life (unguided therapy) and after the 3-week intervention period. To standardize the training content as much as possible, the therapists involved in the study will be trained before the start of the study. During 5 standardization training sessions, the intervention guideline will be discussed, explicated, and the therapists will be trained with the help of example cases. During the trial, therapists will attend 3 evaluation sessions to discuss the progress of the study and possible cases or difficulties they may experience during the intervention.

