Second, in this study, the motor learning conditions are tailored to the individual participants. Most implicit motor learning studies use strict research protocols in which each participant usually receives the exact same instructions (eg, the whole experimental group receives the same right-angled triangle analogy to learn topspin forehand in table tennis), whereas the explicit learning is promoted by using the same set of verbal instructions [24]. A one-size-fits-all approach may not be ideal for the clinical population as they generally demonstrate a large variety in degree and types of impairments. The use of personalized analogies allows the physiotherapists to respond to the individual walking impairments and emphasize on the meaningful component of analogy learning. With a personalized approach (more comparable with the real-life practice), the instructions may be less standardized. Therefore, steps were undertaken to ensure the quality of the interventions. Before the study, all therapists were familiarized and trained with the implicit and explicit conditions. Measures (therapists’ logs and audio recordings of the interventions) were selected to evaluate whether the trainings were delivered as intended, and data will be analyzed as per the intention-to-treat and per-protocol (see the Data Analyses section).

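### The Data Analyses section contradicts itself on who is analysed: attenders of at least 7 of 9 sessions, or everyone as allocated

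*Protocol article*

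**What the plan says.** All the conflicting statements except the last stand in the Data Analyses section of the protocol article.

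- First paragraph, on who enters the statistical analysis: "Only data of the participants who attended minimum of 7 or more of the therapy sessions will be considered as adherent and processed". The sentences that follow describe the group comparison, the repeated-measures analysis at three time points, the post hoc tests and the comparison with the MCID. None of them limits the attendance condition to a secondary set.
- Second paragraph: "Data will be analyzed according to an intention-to-treat and per-protocol principle". It goes on: "In the intention-to-treat, data of the participants are analyzed according to their original treatment allocation".
- Per-protocol has its own trigger, namely fidelity data showing that "cases are not delivered as intended, then the analyses will be performed using the per-protocol principle". It also has its own exclusion, based on deviations in two or more sessions: "If protocol deviations were observed, then data from this person were not included in the per-protocol analysis".
- The Discussion (From Laboratory Setting to Clinical Practice) repeats that "data will be analyzed as per the intention-to-treat and per-protocol".

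The threshold is 7 of 9, because "All participants will receive 9 training sessions in a 3-week intervention period" (Training of Therapists and Treatment of Participants). Anyone with six or fewer sessions falls under the rule.

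**The concern.** A set restricted to good attenders cannot also be the set of all participants as allocated. The plan states both, and a reader cannot tell which one yields the primary result.

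This matters because attendance is observed after randomisation. If the arms lose different proportions of participants to the 7-session rule, or different kinds of participants, the groups compared are no longer those that randomisation formed. The restricted result could then be reported as intention-to-treat when it is not. The arms are designed to contrast as strongly as possible and participants will probably know which training they receive (Blinding), so differential attendance is possible. Nothing in the document shows that it will occur.

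**Working it through.** **Step 1: the statements side by side.**

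| Set | Rule | Basis |
|---|---|---|
| Statistical analysis (paragraph 1) | at least 7 of 9 sessions (78%) | participant attendance |
| Intention-to-treat (paragraph 2) | original allocation | randomisation |
| Per-protocol (paragraph 2) | no deviations in two or more sessions | delivery by the therapist |

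The first row cannot be read as the definition of the third, because their criteria differ. The intention-to-treat sentence says in which arm a person is counted. It does not say that people removed by the first row come back. The conflict therefore stands without any calculation.

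**Step 2: the plan's own figure.** Inputs from Sample Size: difference 0.16 m/s, SD 0.23 m/s, alpha 0.05 (two-sided assumed), power 0.80.

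n = 2 × [0.23 × (1.960 + 0.842) / 0.16]² = 32.4, rounded up to 33 per group. Then 33 × 1.2 = 39.6, rounded up to 40. Both figures reproduce, and the contradiction does not change them.

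**Step 3: how large the bias could be.** The documents give no attendance rates and no link between attendance and outcome, so these inputs are assumptions:

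- 40 per arm and no true difference.
- T0–T1 correlation 0.8, so change SD = 0.23 × √(2 × (1 − 0.8)) = 0.145 m/s.
- Participants are excluded when an index made of their change plus noise of equal variance is low. The correlation between change and index is 1/√2, about 0.7.

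If a fraction k of an arm is excluded, the mean of those retained rises by 0.707 × 0.145 × φ(z_k) / (1 − k), where φ(z_k) is the standard normal density at the k-quantile.

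| k | φ(z_k) / (1 − k) | rise in arm mean (m/s) |
|---|---|---|
| 5% | 0.1031 / 0.95 = 0.109 | 0.011 |
| 10% | 0.1755 / 0.90 = 0.195 | 0.020 |
| 15% | 0.2332 / 0.85 = 0.274 | 0.028 |
| 20% | 0.2800 / 0.80 = 0.350 | 0.036 |

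The bias is the difference between the two arms' rises. Type I errors are from simulation.

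| Excluded, arm A vs arm B | Bias (m/s) | Share of 0.16 m/s | Type I error |
|---|---|---|---|
| equal in both | 0 | 0% | about 5% |
| 20% vs 10% | 0.036 − 0.020 = 0.016 (0.015 to 0.016 in simulation) | about 10% | 7% to 8% |
| 10% vs 0% | 0.020 | about 12% | 9% to 10% |
| 20% vs 0% | 0.036 | about 22% | about 19% |

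The 5% for equal exclusion and the 7% to 8% for 20% vs 10% use a fixed cut-off on the index. Dropping a fixed number of the lowest-ranked participants instead leaves the bias almost unchanged and gives somewhat higher type I errors, 6% to 7% with equal exclusion.

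**Step 4: a different assumed mechanism.** Suppose excluded participants differ from retained ones by s in mean walking speed, with no difference between the full arms. The bias is then s × (difference in exclusion rates). With s = 0.23 m/s and 5% vs 20%, it is 0.23 × 0.15 = 0.0345 m/s, with type I error about 10%. With 10% vs 30%, it is 0.23 × 0.20 = 0.046 m/s, with about 12%. With equal rates it is zero. The as-allocated comparison keeps about 5% throughout.

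**The case against.** The strongest objection is that the document commits to intention-to-treat in two places and defines it by allocation. If the second paragraph governs, a comparison of everyone as allocated exists and the 7-session sentence is a misplaced description of adherence. The word adherent does belong to per-protocol vocabulary. This stands as far as it goes. A reader might infer that the main comparison is definitely restricted to completers and that no unbiased test of the research question remains, but the text does not settle that. The set is also one of adherers, not completers, since attending sessions and providing outcome data are separate matters. The objection does not remove the conflict: the attendance sentence is unqualified, comes directly before the description of the main analysis, and differs from the per-protocol rule.

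A second objection concerns size, and it stands. The larger figures need markedly unequal exclusion. The plan's only attrition figure, 20%, combines dropout and loss to follow-up (Sample Size) and is not a low-attendance rate. Both arms have the same number and length of home sessions, and training in both is tailored to what is feasible for the participant. A claim that one arm would tire people more is speculation.

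Third, a reader might infer that low attenders go unassessed after the intervention. No section says so, and Measurements schedules the assessments without an attendance condition.

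Finally, the objection that an article condenses a fuller plan does not apply. The issue is a rule that is stated and conflicts with another, not detail left out.

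**Conclusion.** The contradiction is real and should be resolved before analysis, because it decides who enters the walking-speed comparison. The consequence is conditional: if the first paragraph is applied literally, the result called intention-to-treat is filtered on post-randomisation attendance and may be biased.

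The documents do not fix the size. Under the main set of assumptions it runs from 0 with equal exclusion, through about 0.015 to 0.016 m/s at 20% against 10%, to about 0.036 m/s with type I error near 19% at 20% against none. The last is a one-arm worst case within that model, not a forecast. The alternative mechanism gives 0 to 0.046 m/s under its own assumptions. The case for changing the text rests on the wording, not on these figures.

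**What to change.** In Data Analyses:

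1. Delete the 7-session condition from the general description of the statistical analysis.
2. State that the primary analysis includes all randomised participants in the group to which they were allocated, whatever number of sessions they attended, using all available T1 and T2 data.
3. Place the attendance condition in the per-protocol definition, beside the delivery-deviation rule, or in a named sensitivity analysis.
4. Report that analysis alongside the intention-to-treat analysis. The same paragraph now both promises per-protocol outright and makes it depend on the fidelity data, and one sentence can settle this too.

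The cost is a change of wording. The assessments are already scheduled for everyone. The estimate may be slightly diluted by low attenders. As an extreme illustration, if 10% of participants contributed no between-group difference at all, 0.16 m/s would become 0.9 × 0.16 = 0.144 m/s. With all 40 per arm analysed, power would be Φ(0.144 / (0.23 × √(2/40)) − 1.96) = Φ(0.84), about 80%. Without dilution it is 87.5%. Removing 20% of each arm (32 left) gives 79.5% at the undiluted 0.16 m/s.

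### Pre-randomisation T0 walking speed is analysed as an outcome level rather than a covariate, which is less efficient and, depending on the term read, may fall short of the stated 80% power

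*Protocol article*

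**What the plan says.** Study Design places the baseline measures before randomisation, with follow-up directly after the intervention (T1) and one month later (T2). Table 1 lists the 10-meter walking test (10MWT) at all three.

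Data Analyses then states: "A repeated measure analyses will be used to compare the 2 groups (implicit and explicit) at 3 different time points", and spells these out as before, after and one-month follow-up. It adds: "Post hoc tests with correction for multiple testing will be used to explore effects over time and between groups", and: "An alpha level of .05 will be set for all tests". Apart from their place in this model, baseline scores are mentioned only for comparing the two groups. The primary outcome will also be described against a between-group difference of 0.16 m/s.

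Sample Size sets out a single two-group comparison: "The power is set at beta=.80, the significance level at alpha=.05, and a standard deviation of 0.23 m/s". For the effect, "the minimal clinically important difference (MCID) is used and set at a minimum change of 0.16 m/s". The result is 33 per group, with 40 to be recruited. The research question asks whether the 3-week implicit intervention is more effective on walking speed. It does not say at which follow-up visit.

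**The concern.** No treatment effect can exist at T0. Making T0 a third outcome level therefore has consequences for each term that the model offers:

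- The group main effect averages in a zero. An effect of 0.16 m/s at both T1 and T2 becomes 0.107 m/s.
- The group-by-time interaction is a 2-df omnibus test. It does not itself give a difference in m/s to set against 0.16.
- A group difference at T1 or T2 comes from a further contrast, and the post hoc contrasts described carry a correction that the sample size did not allow for.

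Baseline 10MWT speed, a natural covariate for follow-up speed, is collected but not used as one. At stake are precision, the match between the powered test and the reported test, and clarity about which of several results answers the research question.

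**Working it through.** **Inputs from the document.** Difference 0.16 m/s, SD 0.23 m/s, alpha .05, power 80% (written as a beta of .80), equal groups, 33 per group needed, 40 recruited, 20% loss (all from Sample Size).

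**Assumptions.** The document gives no correlation r between visits, so a range is shown. Other assumptions are equal correlation between all visits (compound symmetry), Bonferroni for the unspecified correction, and two-sided tests. 0.23 is first taken as the SD of speed at one visit. The number analysed is 0.8 × 40 = 32 per group.

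**The plan's own figure.** n = 2 × [0.23 × (1.960 + 0.842) / 0.16]² = 32.4, so 33 per group. This reproduces the stated size: one two-sided comparison, unadjusted for baseline and for multiplicity. A one-sided test would give 26. The same test with 32 per group has t-test power 0.78.

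**1. Corrected raw group test at T1 or T2.** Standardised difference 0.16/0.23 = 0.696; noncentrality 0.16 / (0.23 × √(2/32)) = 2.78.

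| Tests corrected for | Alpha | Power |
|---|---|---|
| 2 | .025 | 0.69 |
| 3 | .0167 | 0.63 |

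By the normal approximation, 80% power would need 40 (two tests) or 44 (three tests) analysed per group.

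**2. Group main effect over T0, T1 and T2.** The effect is (0 + 0.16 + 0.16)/3 = 0.107; the SD of a participant's mean is 0.23 × √((1 + 2r)/3).

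| r | SD of mean | Power |
|---|---|---|
| 0.5 | 0.188 | 0.61 |
| 0.7 | 0.206 | 0.53 |
| 0.8 | 0.214 | 0.50 |
| 0.9 | 0.222 | 0.47 |

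**3. Group-by-time interaction (2 df).** Noncentrality = (n/2) × Σ(δ − mean δ)² / [0.23² × (1 − r)], with δ the group difference at each visit and 2 × (2n − 2) = 124 denominator df. For δ = (0, 0.16, 0.16) and r = 0.5: 16 × 0.01707 / 0.02645 = 10.3.

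| Pattern of effect | r = 0.5 | r = 0.7 | r = 0.8 |
|---|---|---|---|
| Sustained to T2 | 0.82 | 0.97 | over 0.99 |
| Halved by T2 | 0.69 | 0.90 | 0.98 |

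The sum of squares is the same for (0, 0.16, 0.16) and (0, 0.16, 0). The test therefore has the same power whether the effect lasts or vanishes by T2, and a significant result does not tell the two apart.

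**4. One baseline-adjusted contrast at alpha .05.** If 0.23 is the SD at one visit, the residual SD is 0.23 × √(1 − r²). If 0.23 is the SD of change, the residual SD is 0.23 × √((1 + r)/2).

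| r | 0.23 = SD at one visit | 0.23 = SD of change |
|---|---|---|
| 0.5 | 0.89 | 0.89 |
| 0.7 | 0.97 | 0.84 |
| 0.8 | 0.995 | 0.82 |

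Under the second reading, the 0.69 and 0.63 of step 1 become the power of corrected tests of change from T0.

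**The case against.** The strongest reply is that repeated measures with baseline as a level is valid under randomisation. It brings no bias, and the interaction keeps its type I error. That stands: the point is about efficiency.

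A reader might go further and infer any of three things that the article does not support.

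- *That baseline information is thrown away.* It is not. The interaction and any change-from-T0 contrast use T0 by differencing. Only the group main effect and raw tests at one visit fail to exploit it.
- *That the group comparison is reached only through corrected post hoc tests, so power is below 80%.* The article says that the repeated measures analysis itself compares the groups, and that the post hoc tests are there to explore. The interaction exceeds 80% at r of 0.5 or more if the effect is sustained. Change tests corrected for two comparisons reach about 0.90 at r = 0.7 if 0.23 is the SD at one visit.
- *That "An alpha level of .05 will be set for all tests" contradicts the correction.* Adjusted p-values judged against .05 satisfy both statements.

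It is also fair to say that the number of post hoc tests, the type of correction and the covariance structure may be left to an analysis plan that is not shown. Their absence is not held against the article. What remains is what it does state: T0 as an outcome level, corrected between-group contrasts, and a sample size for one uncorrected test.

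Finally, one-month durability is an explicit hypothesis in the Discussion, so choosing T1 over T2 as primary is a design decision, not mere wording.

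**Conclusion.** The point holds as an efficiency improvement; the analysis is not invalid. With 32 per group, power for 0.16 m/s runs from 0.47 to over 0.99 across the terms the plan could report, according to the term and the assumed correlation. Corrected raw tests and the group main effect fall below the stated 80% (the latter over r = 0.5 to 0.9), while the interaction does so in some scenarios only, such as 0.69 at r = 0.5 when the effect halves by T2. A shortfall is therefore possible, not established.

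One baseline-adjusted contrast at .05 stays above 80% in every scenario tabulated. Its margin rests on how 0.23 is read: power rises with r to 0.995 if it is the SD at one visit, but declines from 0.89 to 0.82 if it is the SD of change. The article does not say which applies. All these figures also rest on the assumed correlations, compound symmetry (steps 2 and 3) and Bonferroni (step 1).

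**What to change.** Before the data are analysed, replace the repeated measures sentence along these lines: 10MWT speed at T1 and T2 will be analysed in a linear mixed model with T0 speed as a covariate and group, time and group-by-time as fixed effects. The primary result is one baseline-adjusted group difference, tested at two-sided alpha .05 and reported with its 95% confidence interval, which can be set directly against 0.16 m/s. The multiplicity correction applies only to the remaining contrasts.

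T1 fits the 3-week research question. The sponsor should confirm that choice, given the one-month durability hypothesis. It would also help to state whether 0.23 m/s is the SD at one visit or of change.

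Cost: no new data and no more participants, since T0 speed is already collected. The downside is that the time point not chosen becomes secondary.
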